## Methods

### Study design

This study will be a prospective, single-blind, randomized controlled trial conducted in Beijing Chaoyang Hospital. The measurements of several outcomes will be made before and after the interventions and 24 weeks after the interventions begin (Fig. 1). This study was approved by the Ethics Committee of Beijing Sport University (Ethics Approval No. 2020108H) and registered at the Chinese Clinical Trial Registry (ChiCTR2000037859). We designed this study using the Standard Protocol Items: Recommendations for Interventional Trials (SPIRIT) statement [28] (Fig. 2). The results will be reported in accordance with the CONsolidated Standards of Reporting Trials (CONSORT) guidelines [29]. The participants will be informed that the trial will not collect any biological specimens for storage. This process will be carried out by researchers blinded to group allocation.

**Fig. 1 Fig1:**
[figure not shown]
Flow diagram of the planned study. KOA, knee osteoarthritis; LL, low load; BFR, blood flow restriction; HE, health education

**Fig. 2 Fig2:**
[figure not shown]
Schedule of enrollment, intervention, and assessment (SPIRIT figure). LL, low load; BFR, blood flow restriction

### Participants

In this study, we will recruit 100 male and female patients with a diagnosis of unilateral or bilateral KOA. For participants with bilateral KOA, the affected side with worse Kellgren-Lawrence grade will be identified as the affected leg. The participants will then be randomly assigned to different interventions. The recruitment of participants will conduct through targeted strategies, including social media (WeChat), websites, newspapers, and other community approaches. If an interested patient meets the eligibility criteria, then the informed consent process will be performed by researchers who are blinded to group allocation. All potential participants will be informed that the study will last for 6 months, that they have the right to withdraw at any time, and that the trial will not collect any biological specimens for storage. If they are uncertain whether they will be able to participate for the entire 6-month period, we will provide regular healthcare for their KOA rather than include them in the formal study. All participants will be asked to provide written informed consent before the intervention. Figure 1 demonstrates the flow chart for the trial, which includes participant recruitment, eligibility screening, baseline measurements, randomization and allocation, intervention, and outcome assessments. The enrollment of participants, the randomization procedure, and the performance of various measurements will be conducted by four independent physiotherapists. A manual will be developed to standardize the administration of the subjective questionnaires and the objective performance tests.

#### Inclusion criteria

The inclusion criteria will be as follows: (1) 45–75 years of age, (2) unilateral or bilateral KOA diagnosed according to the American College of Rheumatology clinical classification system [14, 30], (3) radiologic confirmation of KOA demonstrating Kellgren-Lawrence grade II or III [31], (4) average pain intensity of 40 or more on a 100-mm visual analogue scale (VAS) in the past week, and (5) adequate Mandarin language skills to complete the Western Ontario and McMaster Universities Osteoarthritis Index (WOMAC) and the written informed consent.

#### Exclusion criteria

The exclusion criteria will be as follows: (1) a history of knee surgery or scheduled surgery, (2) a history of any invasive procedure in the affected knee, including arthroscopy or intra-articular injection in the past 12 months, (3) a history of physical therapy/physiotherapy or a strengthening procedure of the affected knee in the past 6 months, (4) use of nonsteroidal anti-inflammatory drugs in the past 3 months, (5) any neurological, heart, or vascular disease, such as blood coagulation disorders, (6) abnormal blood pressure (resting systolic blood pressure [SBP] > 160 or < 100 mmHg or diastolic blood pressure [DBP] > 100 mmHg), or (7) other acute or chronic disorders or psychiatric conditions that will affect physical or cognitive functions.

### Withdrawal criteria and management

The KOA patients will be asked, or be allowed, to quit the study in the following cases: (1) the participants demand it and (2) there is a severe adverse event during the study.

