### Intervention

All participants in the intervention groups will complete 24 exercise sessions over 12 weeks, with two sessions per week, as described in Table 1. During the 12 weeks, the participants may continue their previous activities without aggravating their knee symptoms. In an individual exercise session, each group will perform a warm-up exercise to prevent injuries before the formal exercise protocol. Moreover, the pain intensity will be monitored using a VAS during the exercise, with some pain considered as acceptable. However, the load will be decreased by 20% if the pain intensity is higher than 20 mm/100 mm on the VAS [32]. During the period of intervention, all participants are not allowed to accept any other form of therapy, including medications.

**Table 1 Tab1:** Treatment protocol performed by the LL group and the BFR groups

LL group and BFR groups	
• Hamstrings stretching, 3 repetitions of 30 s	
• Bridge with isometric contraction of the transversus abdominis-CORE training, 3 repetitions of 30 s^+^	
• Hip abduction with weights (side lying), 3 sets of 10 repetitions^+^	
• Calm exercises (side lying) with an elastic band, 3 sets of 10 repetitions^+^	
• Calf raises with weights (standing), 3 sets of 10 repetitions^+^	
• Sensori-motor training (standing) at mini-trampoline, 3 repetitions of 30 s	
• Leg press (machine), 0–60°, 3 sets of 15 repetitions*	
• Seated knee extension (machine), 90°–0° of knee flexion, 3 sets of 15 repetitions*	

*Load is 30% of the 1-repetition maximum

^+^The load will be adjusted every 4 weeks to maintain an effort of perception between 6 and 7 on the Borg scale

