### Outcome measures

#### Primary outcome measure

Pain

A VAS will be used to evaluate pain intensity at rest and under maximum situations during the last week. The VAS comprises a line with a length of 100 mm, in which “0 mm” corresponds to no pain and “100 mm” to the worst pain imaginable [40]. The VAS depicts pain effectively and is easily operated and widely applied in patients with KOA. The VAS will be evaluated at baseline and 12 and 24 weeks after the randomization of the participants. Notably, the minimal clinically important improvement for pain is about 20 mm/100 mm [41].

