### Sample size estimation

Previous studies have shown that the effect size for pain is 0.38–0.49 [52, 53]. The sample size was estimated by using G-Power software (version 3.1.9.6, Heinrich-Heine-Universität Düsseldorf, Düsseldorf, Germany) with the following parameters: analysis of variance (ANOVA) with repeated measures, a type I error of 5% (*α* = 0.05), a power of 95% (*β* = 0.05), group numbers = 4, number of measurements = 3, and effect size = 0.38. The total sample size of this study should be a minimum of 84 participants. With a possible dropout rate of 15%, it is estimated that a sample size of 25 patients per group will be needed to verify our study hypotheses for the primary outcomes.

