### Statistical analyses

All data will be expressed as mean ± standard deviation (SD). A linear mixed model with repeated measures will be run to assess the data for fixed factors of the trial (LL group, High BFR group, Low BFR group, and HE group) and time (primary and secondary outcomes). Additionally, two-way ANOVAs will be used to analyze the differences between baseline, post-intervention, and follow-up measurements. Data from all subjects will be included in the statistical analyses, and the ITT approach will be applied to avoid disrupting the randomization of groups from dropping out through the trial. Any subject who started treatment will be included in the final outcome analysis regardless of whether he/she completed the study. Additionally, the missing data will be multiply imputed using chained equations with predictive mean matching, imputing data for each group separately. Estimates from 10 imputed data sets were combined using Rubin’s rules [54]. The level of significance will be set at *P* < 0.05 for all data. Statistical analyses will be performed using SPSS 22.0 (SPSS Inc., Chicago, USA).

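### A severe adverse event may end study follow-up as well as training, leaving the 12- and 24-week pain and WOMAC values to be imputed from patients in the same arm who stayed

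*Protocol article*

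**What the plan says.** All places are in the protocol article.

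- *Withdrawal criteria and management*: "The KOA patients will be asked, or be allowed, to quit the study in the following cases". Two cases follow: the participant's own demand, and that "there is a severe adverse event during the study". What is left is the study, not the exercise programme. The section gives no route for stopping the programme while staying under observation.
- *Primary outcome measure*: "The VAS will be evaluated at baseline and 12 and 24 weeks after the randomization of the participants". The WOMAC has the same three time points (*Secondary outcome measures*).
- *Intervention*: "All participants in the intervention groups will complete 24 exercise sessions over 12 weeks". No outcome visit for VAS or WOMAC falls between baseline and the end of training.
- *Statistical analyses*: "Any subject who started treatment will be included in the final outcome analysis regardless of whether he/she completed the study". For values that are absent, "the missing data will be multiply imputed using chained equations with predictive mean matching, imputing data for each group separately".
- *Secondary outcome measures*, adverse events: all events are recorded throughout and reported, with a judgement on whether they relate to treatment.

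**The concern.** Stopping a treatment and stopping measurement are different decisions. An intention-to-treat comparison needs outcomes from patients who stopped treatment, whatever the reason. The withdrawal section runs the two together for patients with a severe adverse event.

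A patient who leaves during training has a baseline VAS and nothing after it. The imputation must then supply both later values. Predictive mean matching copies values from observed donors, and imputing each group separately confines the donors to the patient's own arm. If patients with a severe event have left, few or no donors had one. The imputed values therefore describe patients who stayed.

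This matters because the trial compares arms that may differ in harm. The *Background* says that higher occlusion pressure causes more pain during exercise. The *Discussion* presents 40% LOP as a possible choice for patients who cannot bear a high degree of restriction. If severe events were more frequent in one arm, the missing values would flatter that arm in the efficacy contrasts.

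**Working it through.** **Inputs from the article**
- Arm size 25 and all-cause dropout 15% (*Sample size estimation*).
- Important improvement: "the minimal clinically important improvement for pain is about 20 mm/100 mm" (*Primary outcome measure*).

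**Inputs assumed, because the article does not give them**
- k, the number of patients per arm who leave after a severe event during training: 1 or 2, with 4 as an extreme.
- D, how much worse (mm) their true VAS is than the value imputed for them: 20 to 40.

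**The plan's own figure.** A repeated-measures ANOVA, between-groups test, with f = 0.38, 4 groups, 3 measurements, alpha 0.05 and correlation 0.5 (assumed) gives N = 84 with power 0.952. This matches the stated minimum of 84. Allowing for dropout, 84 / 0.85 = 98.8, and 98.8 / 4 = 24.7, so 25 per arm. The point does not change this number. It supplies the denominator below.

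**Shift in one arm's mean.** Let the patients who stay have mean VAS m.
- True arm mean = [(25 − k) × m + k × (m + D)] / 25 = m + kD/25.
- Expected arm mean after same-arm imputation, if the predictors do not capture the deficit = m.
- The arm's mean pain is therefore too low, that is too favourable, by kD/25.

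| k of 25 | D = 20 mm | D = 40 mm |
|---|---|---|
| 1 | 0.8 mm | 1.6 mm |
| 2 | 1.6 mm | 3.2 mm |
| 4 (extreme) | 3.2 mm | 6.4 mm |

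For 1 or 2 patients, the range of 0.8 to 3.2 mm is 0.8/20 = 4% to 3.2/20 = 16% of the important improvement.

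**The extreme row.** 15% of 25 is 3.75, about 4 patients. Reaching k = 4 would require the whole planned dropout of an arm to be severe adverse events.

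**Check by simulation.** Predictive mean matching on baseline within an arm of 25, with 10 imputations and assumed VAS distributions, gave shifts of 1.57 and 3.20 mm for k = 2, and 3.16 and 6.37 mm for k = 4 (D = 20 and 40). The formula gives 1.6, 3.2, 3.2 and 6.4. This confirms the mechanism under the assumed deficit. It is no evidence for the size of k or D.

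**Bias in a contrast.** Bias = (k1 × D1 − k2 × D2) / 25. With D = 20 in both arms:
- two patients against one gives 1.6 − 0.8 = 0.8 mm;
- two against none gives 1.6 mm;
- equal numbers give 0.

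**The case against.** **The wording is partly permissive.** Patients are asked or allowed to leave, and the text does not say that outcome collection ends. The article condenses a full protocol that is not shown, which may cover data collection after training stops. This stands in part: one cannot say that outcomes are lost by rule in every case. But the article does more than stay silent. It states a rule, makes the study the thing left, and offers no alternative.

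**The size is assumed.** There is no severe-event rate, no outcome deficit and no evidence of imbalance between arms. Several listed potential events, such as muscle soreness or numbness, need not worsen knee pain weeks later. This stands, and is why the result is shown as a range.

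**The imputation method is ordinary.** Imputing by randomized group is standard, and matching conditions on predictors. After an event later than week 12, the patient's own 12-week value is available and only week 24 is imputed. This stands too. The remedy is therefore to measure the patients, rather than to condemn the imputation.

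**Stronger readings that the article does not support**
- A reader might infer that patients who merely tolerate the training badly are removed. Intolerance is not a listed ground for leaving: the *Intervention* section answers exercise pain above its VAS limit with a lower load, and the patient continues. Such patients remain among the donors.
- A reader might infer that the trial loses its information on who cannot bear high restriction. Pain during training is monitored in the sessions, and all adverse events are reported. That information survives.
- A reader might apply the 15% dropout to this mechanism. That figure covers all causes, including withdrawal on the participant's own demand.

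**Conclusion.** The point holds in a limited form. As written, a severe adverse event can end a patient's participation in the study. If it occurs during training, both post-baseline VAS and WOMAC values may be missing because of harm and filled from same-arm patients who stayed. The direction is clear if those patients truly do worse than their donors: the arm with more such exits looks too favourable.

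With 1 or 2 such patients of 25 and a deficit of 20 to 40 mm, both assumed, one arm's mean shifts by about 0.8 to 3.2 mm. A contrast is biased only by the difference between the two arms' shifts, which is smaller when both arms have such exits and nil when the shifts are equal. If severe events are rare, the effect is slight.

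The documents do not show that any arm will have more severe events, nor that the intention-to-treat analysis as a whole fails. The problem is confined to the 12- and 24-week efficacy outcomes. It is worth correcting because the correction is cheap and because values never collected cannot be recovered in analysis.

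**What to change.** Amend *Withdrawal criteria and management* so that it distinguishes two events:
1. ending the assigned intervention;
2. withdrawing consent for follow-up.

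State that, after a severe adverse event, the scheduled 12- and 24-week VAS and WOMAC are still collected, remotely if needed, and that only withdrawn consent ends data collection. In *Statistical analyses*, apply the imputation only to what is still missing after that effort.

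The cost is one amended paragraph, a line in the consent form and a little effort to contact the few patients concerned. The questionnaires are already scheduled, and the article reports recruitment as still in progress. When training stops remains a clinical decision, and this change does not touch it.

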### Randomization and allocation concealment

Eligible patients will be randomly assigned to one of the following groups at a ratio of 1:1:1:1: LL group, High BFR (80% LOP) group, Low BFR (40% LOP) group, and HE group. The research staff will independently use SAS software (SAS Institute, Cary, NC, USA) to generate a randomization sequence; this staff will not participate in the intervention or statistical analyses in the study. The number sequence will then be placed into a sequentially numbered, sealed, opaque envelope prior to the study by another independent research assistant who will also not participate in other parts of this study. Once the eligible patients with KOA complete the informed consent process, their demographic information and baseline measures will be recorded. Next, the research coordinator, who will not be involved in the measurement process, will have the authorization to open the envelopes in ascending order to determine a patient’s intervention group assignment.

### Masking

The participants will be informed that all of the interventions have proven efficiencies for their knee disorders, but it is still unknown which intervention works best. Moreover, they will be asked not to discuss their intervention content and group assignment at any time during the study. The intervention locations and times of intervention sessions will be separated for each individual. Unmasking will only be allowed in the case of severe adverse events and will be reported as part of the results of this study.

### Intervention

All participants in the intervention groups will complete 24 exercise sessions over 12 weeks, with two sessions per week, as described in Table 1. During the 12 weeks, the participants may continue their previous activities without aggravating their knee symptoms. In an individual exercise session, each group will perform a warm-up exercise to prevent injuries before the formal exercise protocol. Moreover, the pain intensity will be monitored using a VAS during the exercise, with some pain considered as acceptable. However, the load will be decreased by 20% if the pain intensity is higher than 20 mm/100 mm on the VAS [32]. During the period of intervention, all participants are not allowed to accept any other form of therapy, including medications.

**Table 1 Tab1:** Treatment protocol performed by the LL group and the BFR groups

LL group and BFR groups	
• Hamstrings stretching, 3 repetitions of 30 s	
• Bridge with isometric contraction of the transversus abdominis-CORE training, 3 repetitions of 30 s^+^	
• Hip abduction with weights (side lying), 3 sets of 10 repetitions^+^	
• Calm exercises (side lying) with an elastic band, 3 sets of 10 repetitions^+^	
• Calf raises with weights (standing), 3 sets of 10 repetitions^+^	
• Sensori-motor training (standing) at mini-trampoline, 3 repetitions of 30 s	
• Leg press (machine), 0–60°, 3 sets of 15 repetitions*	
• Seated knee extension (machine), 90°–0° of knee flexion, 3 sets of 15 repetitions*	

*Load is 30% of the 1-repetition maximum

^+^The load will be adjusted every 4 weeks to maintain an effort of perception between 6 and 7 on the Borg scale

Each group will conduct a warm-up by cycling for 10 minutes before the LLRT or BFR training. The leg press will be performed between 0 and 60° of knee flexion, and the leg extension will be performed between 90 and 45° of knee flexion [33]. In addition to thigh muscle strength training, distal joint, proximal joint, and core muscle strength training will also be performed. This is because current evidence has shown that biomechanical changes occur in patients with KOA [34], and a combined multi-joint strength exercise is potentially more effective than knee strength training alone in knee musculoskeletal disorders [35]. To avoid possible injuries during the training, we will provide a relatively integrated therapeutic exercise program. Thus, stretching exercises and core training will also be adopted in this study. During the treatment, we will adopt the 10-point Borg scale to monitor the perceived effort for several exercises [36], as shown in the detailed exercise program in Table 1.

The exercise load will be individually set for each participant and adjusted every 4 weeks by re-evaluating the participant’s 1RM. Since a direct 1RM test could potentially cause knee pain or injury in patients with KOA, the 1RM will be estimated by performing a 7–10 RM test, which is the maximum load that an individual can complete for 7–10 repetitions. Previous studies have shown that the 7–10 RM test can accurately estimate the 1RM for leg press [37] and knee extension exercises [38]. The formula is as follows [39]: estimated 1RM = weight/(1.0278 - 0.0278 × reps).

#### Blood flow restriction exercise groups

All participants from the High BFR and Low BFR groups will be individually measured for the LOP and re-evaluated every 2 weeks during the study. The LOP will be measured with the participants in relaxed and supine positions. The portable color Doppler ultrasound (LOGIQ e, General Electric Company, Boston, USA) will be positioned at the ankle to measure the pedal pulse. A pneumatic cuff (7-cm width and 56-cm length) will be placed on the proximal thigh of the participant and inflated until the pedal pulse vanishes on the Doppler ultrasound. We will then slowly deflate the cuff, and when the pedal pulse returns, we will record the LOP. The Low BFR group will perform at 40% LOP, while the High BFR group will perform at 80% LOP during the exercise. The loads for the leg press and knee extension exercises will be 30% of the 1RM (estimated by 7–10 RM). Furthermore, participants in the High BFR and Low BFR groups will perform one set of 30 repetitions (or until exhaustion) and three sets of 15 receptions with a 30-s interval between sets [20]. The LOP will be adjusted every time to maintain a similar degree of BFR for each individual.

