Blood flow restriction (BFR) training has drawn the attention of clinicians and physiotherapists in the field of musculoskeletal rehabilitation, as it is believed to be an alternative approach to HLRT. In brief, a pneumatized cuff or tourniquet is used to block partial arterial blood flow to the limb, and this is combined with 20–30% 1RM low-load resistance training (LLRT). By creating a state of ischemia in the limbs, BFR training will produce a stronger physiological metabolic stress that includes growth hormones [16, 17] and increased recruitment of type II muscle fibers [18]. Thus, even though the load is relatively low during BFR training, it can still bring increases in muscle strength and mass, similar to the results obtained by HLRT. More importantly, BFR training requires a lower external load, which is beneficial in decreasing the joint loading and tolerance of RT.

Previous studies have found that BFR combined with LLRT yields better improvements in muscle strength compared with LLRT alone in patients with a risk of KOA [19, 20], while its effectiveness in increasing muscle strength, muscle mass, and function in patients with KOA is similar to that of HLRT [21, 22]. Nonetheless, it remains unclear whether the degree of BFR will influence the effectiveness of BFR with LLRT. Many factors contribute to the degree of BFR, including systolic blood pressure, diastolic blood pressure, sex, limb circumference, limb length, and cuff width [23, 24]. The application of limb occlusion pressure (LOP) can produce a more precise degree of arterial occlusion for different individuals compared with absolute air pressure. Only one previous trial has used the percent of LOP to identify the pressure for BFR training in patients with KOA [22]. Notably, 70% LOP BFR training has a similar effect in increasing muscle strength, quadriceps muscle mass, and function compared with HLRT. However, it has been shown that BFR pressures with 40% LOP are as effective as 80% LOP [15] in the acute response of muscles. Nonetheless, the ability to achieve a chronic response with BFR remains unclear, especially for patients with KOA. Additionally, while a higher LOP promotes more pain during exercise with BFR training [25], it seems that pressure with 40% LOP may be more comfortable for individuals compared with 80% LOP, making it beneficial in eliciting compliance to the intervention program.

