#### Low-load resistance exercise group

The LL group will conduct a sham BFR, in which the pneumatic cuff will be placed on the proximal thigh of the participant with adequate space for two or more fingers between the thigh and cuff. However, no pressure will be applied to the pneumatic cuff. The exercise protocol of the LL group is the same as the BFR group. The LL group will perform three sets of 15 repetitions with 30% 1RM and 30-s intervals between sets [19, 21, 32].

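### Leg press and knee extension doses conflict between Table 1 and the BFR section; on the arm-specific text, BFR v LL combines restriction with up to 75 v 45 repetitions per exercise

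*Protocol article*

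**What the plan says.** The dose on the two machine exercises appears in three places in the protocol article.

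- **Intervention, Table 1.** The caption is "Treatment protocol performed by the LL group and the BFR groups", so one list serves all three exercise arms. Its machine rows read "Leg press (machine), 0–60°, 3 sets of 15 repetitions" and "Seated knee extension (machine), 90°–0° of knee flexion, 3 sets of 15 repetitions", with a footnote setting the load at 30% 1RM.
- **Blood flow restriction exercise groups.** After naming leg press and knee extension at 30% 1RM, the section says that participants in both BFR arms "will perform one set of 30 repetitions (or until exhaustion) and three sets of 15 receptions with a 30-s interval between sets". I read the third noun as a misprint for repetitions.
- **Low-load resistance exercise group.** "The exercise protocol of the LL group is the same as the BFR group. The LL group will perform three sets of 15 repetitions", at the same relative load and rest interval.

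The Background explains that the LL arm was included to see whether adding restriction improves on low-load training. Hypothesis 2 predicts that both BFR levels will beat low-load training alone. The Discussion describes the exercise arms as low-load training at pressures of 0%, 40% and 80% LOP.

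**The concern.** The article presents cuff pressure as the difference between the exercise arms, and the LL arm even wears an uninflated cuff to guard against placebo effects. That design isolates restriction only if the rest of the prescription is common. If the BFR arms also receive an additional set on the two machine quadriceps exercises, restriction and repetition volume change together. Every BFR participant is assigned both and no LL participant is assigned either, so neither randomisation nor the analysis model can separate them.

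There is also a plain problem of delivery and replication. A therapist following Table 1 and one following the BFR section would give BFR participants different doses, and a reader could not tell which programme was tested.

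**Working it through.** The article gives no repetition totals, so there is no stated total to reproduce. The check is arithmetic on the prescribed sets and repetitions, followed by a comparison of the texts. The sample-size calculation does not depend on this point.

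**Inputs**

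| Source | LL | BFR 40% and 80% |
|---|---|---|
| Table 1 (Intervention) | 3 × 15 | 3 × 15 |
| BFR section | – | 30 (or fewer, if exhausted) + 3 × 15 |
| LL section | 3 × 15 | described as the same protocol |

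**Step 1: Table 1 delivered.** Each machine exercise has 3 × 15 = 45 repetitions in every exercise arm. The ratio is 45/45 = 1.00.

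**Step 2: arm-specific text delivered.**
- BFR: 30 + 3 × 15 = 75 at most.
- LL: 3 × 15 = 45.
- Difference: 75 − 45 = 30. Ratio: 75/45 = 1.67.
- Two exercises per session: at most 2 × 75 = 150 v 2 × 45 = 90.
- All 24 sessions: at most 24 × 150 = 3600 v 24 × 90 = 2160.

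**Step 3: opening set cut short.** The BFR text allows this set to end at exhaustion, and the article does not say how often or how early that happens. With n completed repetitions in that set, the ratio per machine exercise is (n + 45)/45. The values of n below 30 are assumptions.

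| n | BFR repetitions | Ratio to LL |
|---|---|---|
| 10 (assumed) | 55 | 1.22 |
| 15 (assumed) | 60 | 1.33 |
| 20 (assumed) | 65 | 1.44 |
| 30 (prescribed maximum) | 75 | 1.67 |

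**Step 4: what the LL section's statement of sameness can mean.**
- If it covers only the list of exercises, the BFR and LL sections agree with each other. The error is then in the two machine rows of Table 1, which are wrong for the BFR arms.
- If it covers the full prescription, it fits Table 1 but conflicts with the BFR section, because the LL section's own dose is 3 × 15.

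The BFR and LL sections are specific to their arms, and each cites its own sources for its scheme. Table 1 is one list shared by three arms. This favours the reading in Step 2 but does not prove what is delivered.

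**The case against.** The strongest reply is that a longer opening set in the BFR arms may be a deliberate scheme, since it carries its own citation. On that view specific text governs a shared table, and the only error is two rows that were not split by arm. As an account of the wording this is probably right, but it does not remove the problem. It is the reading under which volumes differ, and neither hypothesis 2 nor the limitations in the Discussion mention volume.

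A second reply is that randomised arms still give a valid comparison of the programmes as prescribed. That stands. What is lost is the attribution of a BFR v LL difference to restriction alone. Hypothesis 1, which compares each exercise arm with health education, remains interpretable as a comparison of programmes.

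Three stronger inferences are tempting, and the document does not support them.

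- **That the pain result is biased by a known amount.** The article gives no figure linking repetition volume to pain, so neither a size nor a clinically important distortion can be claimed.
- **That pain-driven load cuts offset the additional repetitions.** The rule that "the load will be decreased by 20% if the pain intensity is higher than 20 mm/100 mm on the VAS" means a repetition ratio is not a work ratio. But the rule applies to every exercise arm. The Background statement that "a higher LOP promotes more pain during exercise with BFR training" compares higher with lower pressure, not BFR with an uninflated cuff. It gives no basis for assuming cuts in both BFR arms and none in LL, so no load-weighted bound is given here.
- **That the 40% v 80% LOP contrast is confounded in the same way.** Those arms share one prescription. Completed repetitions in the opening set, or the frequency of load cuts, might differ by pressure, but that would be a response to the assigned pressure and not a prescribed difference.

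**Conclusion.** The point holds. Table 1 and the BFR section cannot both be right for the BFR arms, and that follows from the text without assumptions.

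The consequence is conditional. If the BFR and LL sections describe what is delivered, which is the more natural reading, BFR v LL compares restriction plus up to 30 additional repetitions per machine exercise with neither. The BFR v LL part of hypothesis 2 cannot then be concluded as an effect of restriction alone. The ratio of 1.67 is a maximum and depends on the opening set being completed. If Table 1 is delivered, there is no prescribed difference and only the BFR section needs correcting.

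A reader might infer that unequal dosing is established; the document shows only that the prescriptions disagree.

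**What to change.** 1. Establish the set-and-repetition scheme delivered in each exercise arm, and correct Table 1, the BFR section and the LL section to match.
2. If the schemes differ, split the two machine rows of Table 1 by arm and limit the LL section's statement of sameness to the list of exercises. State the BFR v LL part of hypothesis 2, and any conclusion from it, as BFR plus higher prescribed repetition volume versus LL.
3. If delivery has varied within an arm, fix one scheme per arm for later participants, report which scheme each participant received, and analyse by randomised arm.

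The cost is a text amendment while recruitment is still open (Trial status gives completion by February 2022) and, if volumes differ, a narrower BFR v LL conclusion. Some later participants' prescriptions would change only if delivery has varied.
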